## Abstract

**Background:**

A key element in the postoperative phase of the standardized Enhanced Recovery After Surgery (ERAS) treatment pathways is mobilization. Currently, there are no recommendations in the ERAS guidelines for preoperative physical activity. Patients undergoing major surgery are prone to functional decline due to the impairment of muscle, cardiorespiratory, and neurological function as a response to surgical stress. It has been shown that preoperative physical training reduces postoperative complications. To date, there are limited studies that investigate preoperative physical training combined with ERAS.

**Objective:**

The aim of this study is to assess the impact of tailored physical training prior to colorectal surgery conducted according to an ERAS protocol on overall morbidity. This study proposes the initial hypothesis that 3-6 weeks of prehabilitation before elective colorectal surgery may improve postoperative outcome and reduce complication rates, assessed using the Comprehensive Complication Index. The primary objective is to evaluate overall morbidity due to postoperative complications. Additionally, complications are assessed according to the Clavien-Dindo classification, length of stay, readmission rate, mortality rate, and treatment-related costs.

**Methods:**

The prehabilitation Enhanced Recovery After colorectal Surgery (pERACS) study is a single-center, single-blinded prospective randomized controlled trial. Patients scheduled for colorectal resections are randomly assigned either to the prehabilitation group or the control group. All patients are treated with the ERAS pathway for colorectal resections according to a standardized study schedule. Sample size calculation performed by estimating a clinically relevant 25% reduction of postoperative complications (alpha=.05, power 80%, dropout rate of 10%) resulted in 56 randomized patients per group.

**Results:**

Following ethical approval of the study protocol, the first patient was included in June 2016. At this time, a total of 40 patients have been included; 27 patients terminated the study by the end of March 2017. Results are expected to be published in 2018.

**Conclusions:**

The pERACS trial is a single-center, single-blinded prospective randomized controlled trial to assess the impact of tailored physical training prior to colorectal surgery, conducted according to an ERAS protocol, in order to evaluate overall morbidity.

**Trial Registration:**

Clinicaltrials.gov NCT02746731; https://clinicaltrials.gov/ct2/show/NCT02746731 (Archived by WebCite at http://www.webcitation.org/6tzblGwge)

## Introduction

During the 1990s, Henrik Kehlet, a Danish surgeon, developed the concept of fast-track surgery [1]. By optimizing perioperative care, recovery was accelerated. To advance this, the Enhanced Recovery After Surgery (ERAS) concept was developed by Scandinavian and British surgeons. ERAS is an evidence-based multimodal treatment concept to improve postoperative recovery. In contrast to the fast-track concept, the ERAS guidelines do not only focus on pace. Instead, the multifaceted ERAS approach aims to reduce perioperative stress, improve postoperative recovery, reduce morbidity and mortality rates, and shorten the length of hospital stay (LOS). The first ERAS guidelines for elective colorectal surgery were published in 2005 [2].

In the postoperative phase, one of the most important elements pertaining to physical activity is mobilization. According to the ERAS approach, the goal is to get patients out of bed on the same day as the surgery, for at least 4 hours on postoperative day (POD) 1 and for at least 6 hours from POD 2 onwards. However, there are no recommendations for physical activity prior to surgery.

Patients undergoing major surgery are prone to physical decline due to preexisting reduced general health and the impairment of muscle, cardiorespiratory, and neurological function in response to surgical stress. While physically healthy patients have the capacity to cope with this stress response, patients with poorer preoperative physical conditions might not have this capacity. Therefore, these patients are at a higher risk for postoperative complications [3].

In elective cardiac surgery, there is evidence that preoperative physiotherapy reduces postoperative pulmonary complications [4]. Similar effects are suggested for thoracic, abdominal, and major joint replacement surgery [3]. Dronkers at al reported an association between preoperative physical fitness/physical activity and outcome after scheduled major abdominal surgery [5].

To date, there have been only a few studies investigating preoperative physical training combined with ERAS [6]. In respect to existing evidence, which suggests potential benefits through preoperative physical training, one objective of this study is to investigate these findings in the setting of an ERAS approach for colorectal resections. The primary aim of the study is to examine whether moderate to intense physical training (partially supervised by a qualified person), implemented within a short timeframe prior to surgery, will reduce overall morbidity and mortality rates in the ERAS cohort. The hypothesis of the trial is that 3-6 weeks of prehabilitation before elective colorectal surgery improves postoperative outcome.

## Methods

### Study Design

The prehabilitation Enhanced Recovery After Colorectal Surgery (pERACS) trial is a single-center, single-blinded prospective randomized controlled trial to assess the impact of tailored physical training on overall morbidity, prior to colorectal surgery, conducted according to an ERAS approach. Patients with an indication for elective colorectal resection will be randomized into either the intervention group, with preoperative physical training, or the control group without preoperative physical training. Apart from the physiotherapeutic mobilization according to the protocol and ERAS guidelines, all patients will undergo their normal physical activities. All patients will be treated along the ERAS pathway for colorectal resections.

### Patients and Setting

Patients with an indication for elective colorectal resection will be eligible for this study, which will be carried out in the Department of Surgery of the Cantonal Hospital in Winterthur, Switzerland. Patients will be recruited for the study by senior surgeons who will also perform the surgical intervention.

#### Inclusion Criteria

Patients will be included based on the following criteria: adult patients over age 18 with or without comorbidities (eg, diabetes, obesity, cardiovascular disease), patients suffering from colorectal diseases (eg, colorectal cancer, diverticulosis, benign tumors such as polyps or inflammatory bowel disease), patients needing an operative treatment (eg, rectosigmoid resection, anterior resection of rectum, ileocecal/right hemicolectomy, left hemicolectomy, abdominoperineal resection, or total/subtotal colectomy), patients treated according to ERAS, patients undergoing reversal of stoma and Hartmann procedures treated according to ERAS, and informed consent as documented by signature.

#### Exclusion Criteria

Patients will be excluded if they are under age 18, are not able to provide informed consent, have a physical impairment (eg, paresis) or severe cardiac or pulmonary comorbidities (NYHA III or IV), cannot perform the necessary physical training, are not able or willing to attend the physical training at the institute of physiotherapy, are not able to follow the procedures of the study (eg, due to language restrictions, psychological disorders), are participating in another study with investigational drugs 30 days preceding and during the study, or enrollment of the investigator, his/her family members, employees, and other dependent persons.

### Sample Size Calculation

The sample size calculation was performed assuming a clinically relevant 25% reduction of postoperative complications as assessed by the Comprehensive Complication Index (CCI) favoring the treatment group (prehabilitation) when compared to the control group (no prehabilitation) [7,8]. Using a dataset of 47 patients who underwent ERAS colorectal surgery in our department, we determined the mean CCI was 10 (SD 5). Thus, the treatment group mean was set at 7.5, and the standard deviation was adjusted accordingly (SD 3.75) [9]. The alpha error was typically set at .05 and power at 80%. The initial total sample size of 102 patients was increased by 10% to adjust for potential of loss to follow-up resulting in a total sample size of 112 participants (ie, 56 participants per group respectively).

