### Analyses

The statistical analysis will be performed on an intention-to-treat basis by the study’s independent statistician. For each patient, basic demographic, prehabilitation, intraoperative, postoperative, and follow-up data will be generated and stored in a password-protected and encrypted database. These data will be compared separately for each randomization group. Both significant as well as nonsignificant results will be reported accordingly.

The primary endpoint (CCI) will be compared between the two randomized groups (prehabilitation/treatment group vs no prehabilitation/control group) using the Student *t* test. The CCI is known from other trials on postoperative complications to be normally distributed [19,20].

As for the secondary outcomes, the two randomized groups will be compared with the Pearson chi-square test with regards to the Clavien/Dindo classification [21]. This is typically an ordinal variable. Furthermore, the LOS, typically with a skewed distribution, will be compared between the two randomized groups with the Mann-Whitney U test. Readmission and mortality rates will be compared with the Fisher’s exact test between the two groups. The overall total in-hospital costs between the two randomized groups will be compared either with the Student *t* or the Mann-Whitney U-test, depending on their normality of distribution. Cost-effectiveness between the two groups will be compared. All *P* values will be 2-sided and considered statistically significant, if *P*<.05. The statistical analysis will be performed on SPSS 22 for Mac.

A subgroup analysis to investigate whether disease entity (benign vs malignant disease) influences the impact of prehabilitation on the outcome will be performed. Due to the small sample size, further subgroup analysis (eg, for different procedures) will not be performed. There are no multivariable analyses planned for this study due to the nature of the study design (randomized controlled trial) as there will be no need for adjustment of the results.

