## Discussion

### Principal Considerations

Since the introduction of the evidence-based ERAS treatment pathway, the rate of complications has been markedly reduced [22-24]. Equal observations were made in the study center (ie, Cantonal Hospital Winterthur unpublished data). A defining characteristic of ERAS is its multimodal, multidisciplinary approach. One component of ERAS is physical activity, more specifically the early postoperative mobilization of patients. With our study, we aim to investigate the effectiveness of physical training prior to the operation. There is an indication from other areas that physical preconditioning improves the resistibility of patients. The consequence is better toleration of operation-associated stress. However, these findings need to be confirmed for patients with colorectal disorders requiring surgical intervention according to an ERAS approach.

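### The 80% power at 102 evaluable patients depends on a derived treated-arm SD of 3.75; with the observed SD of 5 in both arms it is about 71%, and the SD of 5 itself needs checking

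*Protocol article*

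**What the plan says.** Methods, Sample Size Calculation, sets the target by "assuming a clinically relevant 25% reduction of postoperative complications as assessed by the Comprehensive Complication Index (CCI"). The control inputs come from 47 ERAS colorectal patients treated in the department: "we determined the mean CCI was 10 (SD 5"). For the prehabilitation arm, "the treatment group mean was set at 7.5, and the standard deviation was adjusted accordingly (SD 3.75"), with a literature citation in support. On error rates it says: "The alpha error was typically set at .05 and power at 80"%. The result is 102 evaluable patients, raised by 10% to 112, or 56 per group.

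Methods, Analyses, names the Student t test for the CCI and states that P "values will be 2-sided and considered statistically significant" below .05. The Abstract, Methods, gives the same target in shorter form, as a "clinically relevant 25% reduction of postoperative complications". The Abstract, Objective, words the hypothesis as better outcome and lower complication rates, measured with the CCI. Discussion, Principal Considerations, says that since ERAS was introduced "the rate of complications has been markedly reduced", and that the study center saw the same. No section gives a complication rate.

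**The concern.** Two inputs carry the power statement, and both lean towards a smaller trial.

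The first is the treated SD. Cutting it in proportion to the mean describes a treatment that makes scores about a quarter lower across the board while just as many patients have complications. The stated hypothesis is different: fewer complications. Moving patients from a positive score to zero lowers the mean but tends to keep the spread.

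The second is the control SD. The CCI is obtained by transforming recorded complications, so a patient without any should score 0 and nobody can score below 0. For such an index, an SD of only half the mean leaves little room for patients at zero. That sits uneasily with a pathway described as having lowered complications markedly.

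At stake is how the primary result will be read. If real power for a 2.5-point difference is well below 80%, a nonsignificant result says less against prehabilitation than the stated design suggests.

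**Working it through.** **Inputs.** Control mean 10, SD 5; treated mean 7.5, SD 3.75; difference 2.5; alpha .05; 51 evaluable per arm (Sample Size Calculation). Two-sided Student t test (Analyses). Power is from the noncentral t distribution with 100 degrees of freedom and noncentrality 2.5 / [s × √(2/51)], where s is the root mean square of the two SDs.

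**1. The plan's own figure.** s = √[(5² + 3.75²)/2] = 4.42. Power is 80.8% at 51 per arm and just under 80% at 50. So 51 × 2 = 102, and 102 × 1.10 = 112.2. The stated sizes reproduce.

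**2. Observed SD in both arms.** s = 5. Power at 51 per arm is 70.6%; 80% would need 64 per arm, or 128 evaluable. If all 56 per arm were evaluable, power would be 74.6%. The difference detectable with 80% power at 51 per arm is about (1.984 + 0.845) × 5 × √(2/51) = 2.8 points.

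**3. Fewer complications at unchanged severity.** Suppose a random quarter of complicated patients become complication-free and score 0. Then, whatever the shape of the control distribution:
- control E[X²] = 5² + 10² = 125
- treated E[X²] = 0.75 × 125 = 93.75
- treated variance = 93.75 − 7.5² = 37.5, so SD = 6.12
- s = √[(25 + 37.5)/2] = 5.59, and power is about 61%

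In general, under this mechanism the treated variance is 0.75 × SD² + 0.1875 × mean². The treated SD is therefore always more than √0.75 = 87% of the control SD and cannot reach the 75% that the plan uses. It need not rise, though. At mean 10, a control SD of 10.0 goes to 9.7, and 12.2 goes to 11.5.

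**4. What mean 10 with SD 5 implies.** For an index that is never negative and is 0 without complications, the Cauchy-Schwarz inequality gives

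share above zero ≥ mean² / (mean² + SD²) = 100/125 = 80%,

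with equality only if all complicated patients score the same. The printed values are whole numbers, so the floor is not exact. With 9.5 and 5.49 it is 90.25/120.39 = 75%; with 10.49 and 4.5 it is 110.04/130.29 = 84%. The treated inputs imply the same floor: 56.25/70.31 = 80%.

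**5. Sensitivity only.** The complication shares below are assumptions; the article gives none. The mean is held at 10, and the SD is the smallest that the share allows, √(100/share − 100).

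| Assumed share with complications | Smallest SD | Power at 51 per arm, same SD in both arms | Power with treated SD scaled by 0.75 |
|---|---|---|---|
| 70% | 6.5 | 48% | 58% |
| 60% | 8.2 | 33% | 41% |
| 50% | 10.0 | 24% | 29% |
| 40% | 12.2 | 17% | 21% |

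**The case against.** The best defence is that nothing has been miscalculated. The 102 follows from inputs that are disclosed, and the article defines the effect as a lower CCI, which proportional scaling can represent. The scaling cites a source that is not available here. Nor does an SD of 3.75 require every patient's score to fall by exactly a quarter: any treated distribution with the same ratio of SD to mean would give it. And with equal arms, the Student t test tolerates unequal SDs well. All of this stands. What remains is that the article gives no reason of its own for expecting proportional shrinkage, its hypothesis names complication rates, and about ten points of stated power rest on that choice.

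On the control SD, a reader might infer that mean 10 with SD 5 is impossible, or that true power is only 17% to 33%. The documents do not support either. The SD is reported as observed. All complications are recorded, with no severity threshold stated, so a high share with some event is conceivable. The statement that complications fell markedly is relative and gives no level. The article also does not spell out that a patient without complications scores 0; that is inferred from how the index is obtained. The low power figures depend on assumed rates and on keeping the mean at 10.

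A reader might also infer that preventing complications always leaves the SD the same or larger. Step 3 shows that it can fall, only not by as much as the plan assumes under that mechanism.

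**Conclusion.** The concern holds as a fault in the inputs to the power statement. The stated 80% depends on a treated SD that was derived in the trial's favour and fits poorly with its hypothesis. Taking the department's own SD of 5 at face value, power for 2.5 points at 102 evaluable patients is about 71% with that SD in both arms. It is about 61% if the effect comes from a random quarter of complicated patients having none. These two figures use only the article's mean, SD, effect and sample size; the second also needs a score of 0 without complications.

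The SD of 5 is doubtful but not shown to be wrong. It implies that roughly 75% to 84% of the 47 patients (80% at the printed values) had a complication, which the department can confirm or refute from its own records. If the SD proves larger, power falls below 71%; how far cannot be settled from the article.

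**What to change.** 1. Return to the 47-patient dataset. Report the mean, the SD and the share of zero scores, and confirm that 5 is an SD and not another measure of spread.
2. Restate power and detectable difference for 102 evaluable patients with the control SD in both arms: 71% and about 2.8 points if SD 5 is confirmed, and the less favourable figures if it is larger. Show scenarios with lower complication rates only as labelled sensitivity.
3. At the interim already planned at 56 patients, add a look at the pooled SD blinded to group, used only to update the stated precision.
4. Interpret the primary result through the confidence interval for the CCI difference, so that a nonsignificant result is not read as absence of effect.

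The cost is a re-analysis of data in hand and a less favourable published power figure. No added enrolment is asked for.

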### Intervention

Patients in the intervention group will train for 3-6 weeks prior to surgery, twice a week at the institute of physiotherapy under the guidance of a qualified physiotherapist and once unsupervised at home. Training will be tailored and constantly adapted according to the actual condition of the patient. The program comprises both strengthening and endurance components (see Table 1). In addition, patients will be informed about the importance of their physical condition with respect to the postoperative course and will be encouraged to adhere to the training program, as well as to remain as physically active as possible in addition to the physical exercise training program. Each supervised training session will last 90 minutes and will include the following elements:

Warm-up: guided movements of all main articulations in order to prevent injuries and increasing activity in order to prepare the cardiovascular system for exerciseAerobic interval training on a bicycle: high-intensity interval training with a duration of 32 minutes (4x4mins with 85-90% of maximum training capacity)Resistance training: circuit training on six different devices allowing the strengthening of large muscle groups of the arms and legsCool-down: guided stretching of the previously trained muscles

Patients assigned to the control group receive instructions about the importance of their physical condition with respect to the postoperative course and are encouraged to remain physically active. This is in accordance with the current standard procedure. All patients will be asked to record their physical activity in a diary. Regardless of the group allocation, all patients will be treated according to the ERAS approach.

#### The Steep Ramp Test

The steep ramp test is a validated short maximal exercise capacity test that does not require respiratory gas analysis measurements and has been described in the exercise rehabilitation of patients with chronic heart failure. The main outcome of the steep ramp test is the achieved work rate peak, which partially reflects anaerobic power and leg muscle strength [10]. The test has been proved to be safe, reproducible, and practical in use for prescribing the training load and for monitoring training progress in the rehabilitation of cancer patients [11].

#### 2-Minute Walk Test

The 2-Minute Walk Test is a measurement of endurance by assessing walking distance over 2 minutes. It is a simple test that can be widely used in clinical practice as well as for research [12].

#### Five Times Sit to Stand Test

The Five Times Sit to Stand Test (FTSST) is a quick and easy test to perform. It measures the time (in seconds) that an individual needs to change between sitting (standard chair with arms and a seat height of 43 cm) and standing five times in a row. FTSST is a multidimensional task that is associated with lower extremity strength and balance.

#### Hand Grip Strength

Reduced grip strength has been shown to be a predictor of impaired short-term outcome, such as increased postoperative complications, increased length of hospitalization, higher readmission rate, and decreased physical status [13]. For the grip strength, the average value of three successive measurements of the dominant hand with a Jamar dynamometer [14,15] will be calculated.

#### Fatigue-Visual Analogue Scale

The Fatigue-Visual Analogue Scale (F-VAS) is a horizontal line, 100 mm in length, anchored by word descriptors at each end. Patient mark on the line the point representing their perception of their fatigue. The F-VAS score is determined by measuring in millimeters from the left end of the line to the point that the patient marks.

#### Pain (Numeric Rating Scale)

Level of pain will be assessed by asking patients prior to and after the physiotherapy session to rate their perceived pain intensity using a numeric rating scale (NRS). The NRS is an 11-point scale from 0-10, where “0” indicates no pain and “10” indicates the maximum pain imaginable [16].

#### International Physical Activity Questionnaire ‒ Short Form

The International Physical Activity Questionnaire ‒ short form (IPAQ-SF) will be used in this study because the ease of administration (ie, the burden on participants to report their activity) is small [17]. The IPAQ-SF (9 items) records the activity of four intensity levels: (1) vigorous-intensity activity such as aerobics, (2) moderate-intensity activity such as leisure cycling, (3) walking, and (4) sitting.

